## Abstract

**Background:**

Cognitive rehabilitation is a highly individualised, non-pharmacological intervention for people with mild cognitive impairment (MCI) and dementia, which in recent years has also been developed for various IT platforms.

**Methods:**

In this study, we aim to evaluate the effectiveness of the cognitive rehabilitation software GRADIOR in a multi-centre, single-blinded randomised controlled trial with people with MCI and mild dementia. A total of 400 people with MCI and mild dementia will be randomly allocated to one of four groups. This trial will compare the cognitive rehabilitation treatment using the GRADIOR programme with a psychosocial stimulation intervention (PSS) using the ehcoBUTLER platform, with a combined treatment consisting of GRADIOR and ehcoBUTLER, and with a group receiving treatment as usual during a period of 1 year.

**Discussion:**

The outcomes of this clinical trial will be to determine any relevant changes in cognition, mood, quality of life, activities of daily living and quality of patient-carer relationship after 4 months and 1 year of intervention in a cross-sectional group comparison. Participants will be followed-up for 1 year to investigate potential long-term effects of the conducted treatments.

**Trial registration:**

Current Controlled Trials ISRCTN, ID: 15742788. Registered on 12 June 2017.

**Electronic supplementary material:**

The online version of this article (doi:10.1186/s13063-017-2371-z) contains supplementary material, which is available to authorized users.

## Background

Current prevalence rates of dementia in Spain are approximately 1.75% of the state population, which equates to more than 800,000 people [1]. In their annual report, Alzheimer’s Disease International [2] estimate a prevalence of 1.6 million new cases of dementia per year in people over 60 years of age solely in Western European countries, which is accompanied by increasing costs per capita each year. Mild cognitive impairment (MCI) is a condition with various subtypes of different progression and prognoses, with 20–40% of cases progressing to dementia [3]. The overall crude prevalence of MCI is estimated at around 6–12% at the lower end, with some reviews reporting a prevalence rate of up to 42% in people over 60 years of age [4]. Progressive cognitive deficit, which is present in dementia, restricts the individual independence and the activities of daily living of every person affected [5, 6]. Moreover, it also places high demands on caregivers, family members and health professionals involved in their care [7]. For these reasons, it is important to find a sustainable approach to maintain the independence and self-efficacy of people with dementia (PwD) and MCI. Importantly, cognitive interventions seem to be beneficial not only for PwD, but also for their caregivers [8].

Cognitive rehabilitation is a highly individualised intervention specific to patients’ needs and goals [9], and in people with mild dementia is used to improve or maintain their cognitive status [10]. On the other hand, cognitive trainings are focussed on training or restoration of one particular ability or skill (e.g. working memory, attention, etc.) [11]. Cognitive rehabilitation has shown to be more effective than cognitive training or group reminiscence therapy, having a positive effect on decreasing the functional decline of PwD [12]. Similarly, a systematic review by Clare and Woods reported no significant effects of cognitive training interventions; while the only study on cognitive rehabilitation included in the review found preliminary but promising results of this approach when applied in people with Alzheimer’s disease and vascular dementia [11]. Intensive cognitive rehabilitation programmes can also reduce behavioural disturbances in PwD [13], but their influence on activities of daily living, quality of life or symptoms of depression remains inconclusive [14]. Cognitive rehabilitation can also significantly improve cognition, and reduce behavioural disturbances and symptoms of depression in MCI [15]. Furthermore, cognitive rehabilitation has been proven to have a positive effect in caregivers of PwD by lowering the feeling of burden and improving their confidence in caregiving situations [16].

Computer-based cognitive interventions are a cost-effective and flexible approach which are nowadays easily accessible to the public [17]. Computer-based cognitive trainings have shown to be efficient in people with MCI, which is important when addressing Alzheimer’s disease prevention or delaying the onset of the disease [18]. Currently, the field of cognitive rehabilitation for people with MCI is relatively underdeveloped in comparison to cognitive training. However, studies have shown that computer-based cognitive rehabilitation can also improve general cognition [19], as well as reduce depression and anxiety symptoms in MCI [20]. A meta-analysis by García-Casal et al. [21] reported a significant improvement in cognition, depression and anxiety in PwD involved in computer-based cognitive interventions. Furthermore, it has been reported that computer-based cognitive rehabilitation is able to delay memory deterioration in PwD [22]. People with dementia with low levels of function can also benefit from computer-based rehabilitation programmes which can improve different cognitive domains and mood [23]. Although a different meta-analysis did not reveal any significant changes in cognition for PwD, more studies are necessary in order to discover the potential long-term effects of computer-based cognitive interventions in PwD [24].

Stimulating social activities can serve as an effective prevention strategy in primary care, delaying cognitive deterioration in older PwD and MCI [25]. Psychosocial interventions can also introduce positive changes in cognition, mood or communication in PwD [26] and MCI [27].

GRADIOR is a computer-based programme used for the neuropsychological rehabilitation of people with various cognitive impairments of different aetiology, as well as for cognitive stimulation of healthy individuals. GRADIOR consists of dynamic exercises designed to stimulate all cognitive abilities, offering tools to tailor the cognitive intervention to each person according to their individual needs. The programme also provides tools for the evaluation of the current performance in every cognitive domain, which is important for treatment adjustments (changing difficulty levels for each task independently according to the participants’ performance).

The psychosocial stimulation platform ehcoBUTLER was designed to improve the quality of life of older people and their caregivers by promoting a healthy lifestyle and stimulating active aging through the use of tools that enhance positive emotions and cognitive training [28]. EhcoBUTLER contains leisure activities and other activities focussed on care, and can be adjusted to the needs of every person individually. The aim of all activities is to reduce social isolation, cognitive and physical inactivity and sedentary behaviours, and to promote health, satisfaction and personal wellbeing.

The platform has different versions. The leisure version contains various applications including Wellbeing (Walk), Internet, Book of Life, My Memories (photographs, music and videos), Leisure Activities (books and puzzles) and Social Applications (friends, mail and videoconference). The care version adds activities to each module, such us Nutrition and Lifestyle recommendations, which is part of the Wellbeing module. The platform also facilitates communication and can be used by families and caregivers with the aim of sharing information and keeping up to date with the daily activities or conditions of people. The platform can be used in different devices such as PCs, touch-screen computers and tablets.

Currently, despite the large number of different computer-based cognitive rehabilitation programmes, there is a lack of large-scale randomised controlled trials (RCTs) on individualised cognitive rehabilitation programmes [12]. Furthermore, despite providing initially promising results, the results on the effectiveness of cognitive rehabilitation trainings are still inconclusive and more RCTs are required in this area [29].

For this reason, we will conduct an interviewer-blinded, multi-centre randomised controlled trial with four parallel groups. The primary aim of which is to determine the effectiveness of the cognitive rehabilitation programme GRADIOR and the psychosocial stimulation platform ehcoBUTLER, separately or in a combined treatment, on the cognition, quality of life, activities of daily living, relationships with carers and depressive symptoms of people with MCI and PwD. Based on previous research, we hypothesise that people with MCI and PwD in the cognitive rehabilitation group using GRADIOR or combined treatment will improve their cognition in comparison to other treatment groups and/or the treatment as usual (TAU) group. A secondary aim is to examine the interaction between psychosocial stimulation and cognitive rehabilitation in order to discover their synergies or usefulness. The duration of the RCT is 1 year of treatment followed by a 1-year follow-up study.

A preliminary study on the usability of GRADIOR and ehcoBUTLER will be conducted through focus groups and users’ testing in order to identify any issues in the programme’s features which may potentially influence its effectiveness in MCI and PwD. Additional data will be collected and any incidents will be monitored to improve the final usability of both programmes.

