#### GRADIOR: Computer-based cognitive rehabilitation (GRA)

GRADIOR is a neuropsychological rehabilitation programme activating seven areas of cognitive functions (memory, attention, orientation, perception, calculus, executive functioning and reasoning) with specific tasks. In total, GRADIOR contains 48 different types of exercises with 2 to 11 levels of difficulty (see Appendix). For every participant, the GRADIOR treatment will include exercises for all cognitive subdomains. At the starting point of the treatment, all the participants will receive the same set of exercises which will differ in the level of difficulty for every subdomain based on the participant’s performance in the preliminary baseline treatment.

Participants will attend treatment sessions three to four times per week for 30 min per session. The days or distribution of treatment sessions during the week will depend on the availability of each centre and on the individual availability of participants. The treatment for each participant will be adjusted after 4 months when a midterm assessment will take place. The treatment can also potentially be adjusted before this time based on the participant’s performance in the exercises.

Every exercise in GRADIOR has a duration of 1 min during which different stimuli are presented to the participant who is then asked to provide a specific response (e.g. point only to a certain group of objects). During one treatment session, the exercises are randomised for each subdomain; however, the order of the subdomains in the treatment is fixed. If the participant does not complete all exercises on the list in one session, the subsequent session will pick up from where they stopped, i.e. with tasks for subdomains which are next on the list. In this way, the programme continues in a loop. The user does not repeat the same exercises every session, but only once they have finished the previous set.

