#### ehcoBUTLER: Computer-based psychosocial stimulation (PSS)

EhcoBUTLER is an e-health platform available via the Internet, which aims to promote physical and mental health, social participation, quality of life and personal wellbeing. EhcoBUTLER is aimed at people with MCI or mild dementia as well as their carers.

During the first two sessions participants will be trained to use the system, after which they will use the platform for 5 h per week or more. The time schedule of usage of the platform will depend on each participant and their needs and individual availability. It will be recommended to participants that they use the platform for 2 h per day. To ensure correct usage of the platform, the sessions taking place outside of the participants’ homes will be facilitated by a member of staff. Study coordinators will have access to the data registered by the platform to ensure the participation of all users. On the other hand, the therapist may use the ‘Task List’ function to propose activities to the participants and subsequently monitor their accomplishments.

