#### ehcoBUTLER CARE: Combined treatment (GRADIOR + psychosocial stimulation) (COM)

The group receiving both cognitive rehabilitation and the psychosocial stimulation treatment will have scheduled sessions with GRADIOR twice per week for 30 min per session and will be advised to use ehcoBUTLER for at least 3 h per week. The treatment sessions with GRADIOR will be the same as the group only using GRADIOR and the same procedure will be followed to determine the baseline, adjustments of treatments and levels of difficulty.

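### The aim of finding synergy between GRADIOR and ehcoBUTLER is confounded with dose, because the combined arm is prescribed less of each

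*Protocol article*

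**What the plan says.** The Background of the protocol article sets this aim: "A secondary aim is to examine the interaction between psychosocial stimulation and cognitive rehabilitation in order to discover their synergies or usefulness". The Design section describes four parallel arms allocated 1:1:1:1: GRADIOR (GRA), ehcoBUTLER (PSS), the combination (COM) and treatment as usual (TAU).

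The intervention sections fix the amounts:

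- **GRA:** "Participants will attend treatment sessions three to four times per week for 30 min per session".
- **PSS:** after two training sessions, "they will use the platform for 5 h per week or more". The section adds: "It will be recommended to participants that they use the platform for 2 h per day".
- **COM:** participants "will have scheduled sessions with GRADIOR twice per week for 30 min per session", and are advised to use ehcoBUTLER for 3 h a week or more.

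On GRADIOR content, the COM section says: "The treatment sessions with GRADIOR will be the same as the group only using GRADIOR". The article does not mention, explain or adjust for the difference in amounts, and its Analysis section names no dose term.

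**The concern.** With four arms of this kind, the natural measure of interaction is COM - GRA - PSS + TAU. It isolates synergy only if COM contains each component at the dose given in the corresponding single-component arm. Here COM has a smaller dose of both.

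If benefit rises with dose over these ranges, two components that simply add up would produce a negative contrast. That result could be published as antagonism, or as evidence that combining the programmes brings nothing extra, when it only reflects shorter treatment.

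**Working it through.** The article gives no figure for the interaction aim, so there is none to reproduce. Its Sample size section gives the one effect size used below: 0.30, at 80% power with 340 participants (400 × 0.85 = 340, or 85 per arm).

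**Weekly amounts, from the three intervention sections**

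| | GRADIOR | ehcoBUTLER | Total |
|---|---|---|---|
| GRA | 3 to 4 × 30 = 90 to 120 min | none | 1.5 to 2 h |
| PSS | none | 5 h or more | 5 h or more |
| COM | 2 × 30 = 60 min | 3 h or more | 4 h or more |

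- GRADIOR ratio, COM to GRA: 60/90 = 0.667 and 60/120 = 0.50, so 33 to 50% less.
- ehcoBUTLER ratio, COM to PSS, on the minimums: 3/5 = 0.60, so 40% less. Against 2 h on all seven days (14 h) it would be 3/14 = 0.21.
- Total on the minimums: COM 1 + 3 = 4 h, against 1.5 + 5 = 6.5 h to 2 + 5 = 7 h for GRA plus PSS. The shortfall is 1 - 4/6.5 = 38% to 1 - 4/7 = 43%. COM is also below PSS alone (5 h).

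**What the contrast estimates.** Let g and h be the benefits of GRADIOR and ehcoBUTLER as functions of weekly dose, coded so that positive is better, and let I be the interaction at COM's doses. Then

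COM - GRA - PSS + TAU = [g(60 min) - g(90 to 120 min)] + [h(3 h) - h(5 h)] + I.

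Both brackets vanish only if the doses match or the benefit is flat between them. Estimating g(60 min) or h(3 h) separately needs an arm giving that component alone at that dose, and none exists.

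**Possible size when I = 0.** Assumptions: a GRA effect of 0.30 SD (the article's target effect size), a PSS effect d of 0 to 0.30 SD, and benefit proportional to dose to the power k. The contrast is

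0.30 × (r^k - 1) + d × (0.60^k - 1), with r = 0.667 or 0.50.

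| Dose-response | d = 0 | d = 0.15 | d = 0.30 |
|---|---|---|---|
| Linear, k = 1 | -0.10 to -0.15 | -0.16 to -0.21 | -0.22 to -0.27 |
| Square root, k = 0.5 | -0.06 to -0.09 | not computed | -0.12 to -0.16 |
| Plateau, k = 0 | 0 | 0 | 0 |

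The d = 0 column is the GRADIOR shortfall alone.

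**Precision, for scale.** With 85 per arm, outcome SD 1 and no covariate adjustment, the contrast has SE √(4/85) = 0.217 SD. The effect detectable at 80% power is (1.960 + 0.842) × 0.217 = 0.61 SD.

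**The case against.** The strongest reply is that the article never writes down COM - GRA - PSS + TAU and never calls the design factorial. The interaction in its Analysis section is between inter-subject and intra-subject factors, and the aim may be operationalised in an analysis plan not shown here. The aim also mentions usefulness, which the trial can address. This does not remove the problem: the doses are fixed in the protocol, and no analysis of these four arms supplies the missing single-component doses. Adjusting for logged use would compare people by how much they chose to use the programmes, which is not a randomised comparison.

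Four further points stand, at least in part:

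- The ehcoBUTLER amounts are minimums, so actual use may overlap between PSS and COM. The GRADIOR schedules do not overlap: two sessions against three to four.
- The size of the shift rests on assumed effects and an assumed dose-response, and the range includes zero.
- The contrast is imprecise, so a null result would be weak evidence of no synergy even at matched doses. The dose shift is a separate problem that more participants would not cure.
- If more dose never reduces benefit, both brackets are zero or negative, so a clearly positive contrast would still point to synergy.

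A lighter combined schedule may also be a sensible way to limit burden, although the article does not give that reason. It would make COM a package to be compared as such.

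**Conclusion.** The concern holds. The stated interaction aim cannot be identified from these arms, because COM is prescribed 33 to 50% less GRADIOR and, on the minimums, 40% less ehcoBUTLER. That conclusion needs only the prescribed doses.

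The size of the distortion is conditional. Under the assumed effects and no true interaction it runs from 0 (plateau) to -0.27 SD (linear, both effects 0.30 SD). The upper end is close to the 0.30 the trial is looking for.

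A null or negative contrast could not be interpreted. The reach is limited to this part of one secondary aim. The comparisons of GRA and COM with TAU, and the usefulness of COM as delivered, stand. The point should be corrected, but it does not threaten the primary result.

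**What to change.** Restate the secondary aim as a comparison of the combined package, as delivered, with GRA, PSS and TAU, and drop the claim to identify interaction or synergy. If COM - GRA - PSS + TAU is still reported, label it exploratory, give its confidence interval, and say that COM received less of each component, so a null or negative value is not evidence against synergy. Show logged usage by arm beside it; for ehcoBUTLER the article says "Study coordinators will have access to the data registered by the platform to ensure the participation of all users".

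The cost is the rewording of one aim and a few sentences on reporting. Arms, doses and sample size stay as they are, and the synergy claim is given up. Keeping that claim would require COM at the single-arm doses, 6.5 to 7 h a week on the stated amounts, which is a much heavier schedule for these participants.

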## Methods

### Design

This is a multi-centre, randomised controlled, interviewer-blinded trial, with four parallel groups, 1:1:1:1 allocation ratio. Potential participants will be identified by collaborating professionals at recruitment sites and those interested in participating will sign an informed consent form. Subsequently, those selected based on inclusion/exclusion criteria (*n* = 400) will undergo preliminary testing and will be randomly allocated to one of the four study groups. In this study, there are three intervention groups and one group receiving TAU. Intervention groups are: (1) cognitive rehabilitation with the GRADIOR programme (GRA), (2) a computer-based psychosocial stimulation group (ehcoBUTLER) (PSS) and (3) a group receiving a combined treatment of GRADIOR together with computer-based psychosocial stimulation (ehcoBUTLER CARE) (COM). Primary and secondary measures data will be collected at baseline, at 4 months after the start of the treatment and at 12 months, immediately after completing the interventions. Follow-up assessments will be carried out 4 and 12 months after finishing the treatment (months 16 and 24 of the study). A preliminary study of usability will be conducted before the start of the trial. The full study timeline is described in Table 2.

### Sample size

Maximal sample size for the study was set at 400 participants with dementia and MCI. We considered a 15% dropout by participants during the 12 months of interventions and 12 months of follow-up. Therefore, the final sample size for the study is likely to be 340 participants.

Considering that the standard deviation of the selected population in the selected variables of the study was unknown and the population size was undetermined, we opted for a calculation of the sample size for an infinite population with the maximal level of variability of the dependent variables of the study (*p* = *q* = .5). If the population scattering parameters are unknown, this calculation allows for a more conservative sample size, meaning the biggest sample size [30].

The calculation was executed using the following equation (α = .05):$$ n=\frac{Z_{\raisebox{1ex}{$\propto $}\!\left/ \!\raisebox{-1ex}{$2$}\right.}^2\ast {0.5}^2}{e^2}, $$

where 0.52 is a maximal variability (*p* * (1 − *p*)), *Z*_∞/2_ corresponds to scores in the percentile *α*/2 (.025) of a normal distribution, and *e* corresponds to the error acquired for the desired sample size, with a result of *e* = 5.3% for a sample size of 340 participants.

On the other hand, based on the Friedman table for determining effect size [31], for the primary outcome measure ADASCog to achieve 80% power (alpha 0.05) on a sample of 340 participants we are looking for an approximate effect size of 0.30, which is similar to a separate study protocol on cognitive rehabilitation in PwD [9].

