#### Secondary outcome measures

Changes in quality of life (QoL) scores will be measured using the *EuroQol EQ5D-5 L* [45] which assesses quality of life from five dimensions, and the *Luben Social Network Scale (LSNS)* [46] which looks at social engagement, including relationships with family and friends. QoL scores will be compared between all the intervention groups and with the control group to determine which intervention obtains the best results and most influences the outcome. We will compare scores for each intervention group at 4 and 12 months in order to determine at which point in the treatment the various interventions most influenced quality of life. All participants will be assessed and compared using the *Geriatric Depression Scale (GDS)* [47], a 15-item version of a self-rating scale, in order to determine which type of intervention, if any, has an influence on depressive symptoms in PwD. Demographic data, activities of daily living (instrumental – IADL and non-instrumental – ADL), functional aspects and cost-effectiveness will be assessed using the *InterRAI Home Care* [48]. The quality of the relationship between the participants and their carers will be assessed using the *Quality of Carer-patient Relationship (QCPR) questionnaire* [49].

As GRADIOR focuses solely on cognitive rehabilitation, we assume that those participants with dementia receiving only the GRADIOR treatment will not see improvements in their quality of life, depressive symptoms, the quality of their relationships with a carer and/or activities of daily living after 4 or 12 months.

At the beginning of the study, participants will also receive the *Everyday Technology Use Questionnaire (ETUQ)* [50]. This will assess their perceptions about technology, difficulties encountered when using technology, and their degree of experience with technology that might be relevant for the study.

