Carers will also be assessed at the same time as participants, whereby we will evaluate the following: their anxiety using the *State-Trait Anxiety Inventory (STAI)* [51], symptoms of depression with the *Beck Depression Inventory II (BDI-II)* [52], carer overload using the *Caregiver Burden Interview – Zarit Test* [53] and the quality of their relationships using the *Quality of Carer-patient Relationship (QCPR*) *questionnaire* [49]. We anticipate that GRADIOR will positively influence carer-outcome measures, and therefore, we hypothesise that in both intervention groups using GRADIOR, caregiver burden, anxiety and depression will decrease, and the relationship between the carer and the PwD will improve.

The data collected from the InterRAI Home Care Assessment will be used to analyse the cost-effectiveness of the treatment and its impact on health. The economic evaluation will employ a cost-consequences framework evaluating the associated costs and outcomes of the three types of interventions, in comparison to usual care. The evaluation will also assess the main sources of costs associated with the interventions. Primary analysis will be based on the most plausible real-world costs, including the cost of the technology and technical progress. The support costs for GRADIOR and ehcoBUTLER associated with technical aspects of installation, maintenance of hardware and information, as well as communication technology input related to software and data management, will be based on data gathered from sites. This will also include the input of professionals for guiding participants and support provided to participants throughout the intervention. For a complete list of the assessment tests used and the time schedule see Tables 2 and 3 respectively.

**Table 2 Tab2:** Assessments

Activity/assessment	Staff member	Time	Pre-study	Pre-study baseline	2	4	6	8	10	12	16	24
Usability study	Interviewer	N/A	X									
Focus group		90										
SUS		N/A										
Consent Form	Study coordinator	5	X	X		X				X	X	X
Inclusion/exclusion criteria	Study coordinator	N/A	X									
DSM-5 criteria	Interviewer	N/A	X									
Cognitive assessment	Interviewer	106										
MMSE		20		X		X				X	X	X
ADASCog		40		X		X				X	X	X
WAIS III: Calculus		5		X		X				X	X	X
WAIS III: Digit Span		5		X		X				X	X	X
WAIS III: Coding digit symbol		2		X		X				X	X	X
TMT A and B		10		X		X				X	X	X
Semantic and phonologic verbal fluency		4		X		X				X	X	X
CAMCog matrices		5		X		X				X	X	X

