### Analysis

Statistical analysis will be conducted using programme IBM SPSS v.23. A descriptive analysis of demographic and personal data will be conducted and results will be compared between all groups. Firstly, an analysis of normality and homogeneity of the data will be conducted. For normally distributed data, the repeated measures analysis of variance (ANOVA) will be used to examine the hypotheses in inter-subject and intra-subject analysis as well as in their interaction. This will be applied to all outcome measures in a comparative analysis of the data collected at from baseline, after 4 months and 12 months of the treatment. In case of non-homogeneous data, non-parametric methods will be used for analysis (Mann–Whitney *U* test, Kruskal-Wallis analysis of variance, Wilcoxon signed-rank test, calculation of Spearman’s correlation coefficient, etc.). Bonferroni/Dunnet corrections will be applied during post-hoc analysis if needed. The possible effects of randomisation bias will be analysed using linear-mixed models including within-group and between-group factors. The significance level will be set at *α* = .05.

Effect sizes and their respective standard errors (SE) and confidence intervals will be estimated as Standardised Mean Change Index (dMR) for within-group comparisons, and as Standardised Mean Index difference (dC) for between-group comparisons, and corrected for small sample sizes [54]:

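### Secondary statements worded for people with dementia have no matching analysis: the sample is a pooled MCI-plus-dementia total with no stated split, and no diagnosis factor is named

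*Protocol article*

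**What the plan says.** **Sample size.** One total covers both diagnoses: "Maximal sample size for the study was set at 400 participants with dementia and MCI". No number, quota or minimum is given for either. Then "We considered a 15% dropout by participants during the 12 months of interventions and 12 months of follow-up", so that "the final sample size for the study is likely to be 340 participants". The power statement is "80% power (alpha 0.05) on a sample of 340 participants" for an effect of about 0.30 on the ADASCog.

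**Secondary outcome measures.** Three statements mention people with dementia.
- All participants are compared on the Geriatric Depression Scale "in order to determine which type of intervention, if any, has an influence on depressive symptoms in PwD".
- The investigators assume that "those participants with dementia receiving only the GRADIOR treatment will not see improvements in their quality of life", and likewise for depressive symptoms, carer relationship and activities of daily living.
- The carer hypothesis for both GRADIOR arms ends by predicting that "the relationship between the carer and the PwD will improve".

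**Analysis.** Repeated-measures ANOVA is planned on baseline, month 4 and month 12: "This will be applied to all outcome measures in a comparative analysis of the data collected". No diagnosis factor, arm-by-diagnosis term or dementia-only analysis is named.

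**Participants.** MCI and mild dementia have separate entry criteria, with different CDR and MMSE limits, so every participant's diagnosis is known before randomisation.

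**The concern.** The population analysed and the population of the conclusion differ. This is plainest in the depression sentence, which compares everyone in order to learn about dementia alone. Balanced arms or a diagnosis main effect would not cure this, because the arm contrast would still be an average over the recruited mix. Only a contrast that lets the treatment effect differ by diagnosis gives the effect in dementia.

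Three errors could follow:
- A pooled gain produced by MCI participants is reported as a benefit in dementia.
- A pooled gain produced by MCI participants is taken to refute the no-improvement assumption, although that assumption is true in dementia.
- A non-significant pooled contrast is taken to confirm the no-improvement assumption, which a null result does not do.

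**Working it through.** **Inputs from the article.** 400 randomised, 15% dropout, four arms at 1:1:1:1, alpha .05 with the .025 percentile (two-sided), effect size 0.30.

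**Assumptions.** The metric of the 0.30 is not stated; I read it as a standardised mean difference (SD = 1). The dementia share is not stated; I use a range. Dropout is equal across arms and diagnoses.

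**1. The plan's own figures.**
- 400 × (1 − 0.15) = 340.
- e = 1.96 × 0.5 / √340 = 5.3%, as stated.
- Power comes from the two-sample t-test with non-centrality d × √(n/2), n per group.
- 170 v 170: 0.30 × √85 = 2.77, power 79%. This is close to the stated 80%.
- 85 v 85 (one arm against another): 0.30 × √42.5 = 1.96, power 49%.

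On this reading the stated power is recovered only when all 340 participants, both diagnoses together, are divided into two halves.

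**2. What a pooled contrast estimates.** With dementia share s,

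pooled effect = s × (effect in dementia) + (1 − s) × (effect in MCI).

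Take, for illustration, 0.50 SD in MCI and zero in dementia, at 85 v 85:

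| Dementia share | Pooled effect | Non-centrality | Pooled test significant |
|---|---|---|---|
| 20% | 0.80 × 0.50 = 0.40 | 2.61 | 74% |
| 35% | 0.65 × 0.50 = 0.325 | 2.12 | 56% |
| 50% | 0.50 × 0.50 = 0.25 | 1.63 | 37% |

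For the depression question, these are the chances of a positive result with no effect in dementia. For the no-improvement assumption, they are the chances that a true assumption is wrongly refuted. The risk falls as the dementia share rises.

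**3. What the dementia stratum alone can show.** One arm against another, n per arm = 85 × share:

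| Dementia share | n per arm | Power at 0.30 | Effect detectable at 80% power | Approximate 95% CI half-width, 1.96 × √(2/n) |
|---|---|---|---|---|
| 50% | 42.5 | 28% | 0.61 SD | 0.43 SD |
| 33% | 28.3 | 20% | 0.76 SD | 0.52 SD |
| 25% | 21.25 | 16% | 0.88 SD | 0.60 SD |
| 20% | 17 | 14% | 0.99 SD | 0.67 SD |

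The comparator for the power column is the 49% in step 1, not 80%. Much of the shortfall comes from dividing 340 among four arms; the restriction to dementia takes it from 49% to between 28% and 14%.

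**The case against.** The strongest reply is that this is an omission. Only an article is shown, and factors, interactions and subgroup analyses are commonly left to a full protocol or analysis plan. The Analysis section never names its between-subject factor and also mentions linear mixed models with between-group factors, so diagnosis is not excluded. This stands to the extent that a missing interaction term would not by itself be a finding. It does not remove the mismatch in the text, where a comparison of everyone is said to answer a question about dementia and the power is stated without saying that it is for the pool.

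Three stronger readings are tempting, and the article does not support them.
- *That several hypotheses are restricted to dementia.* Only the no-improvement sentence clearly is. In the depression sentence, PwD may be loose shorthand. The carer hypothesis is mostly unrestricted and names the PwD only in its last clause.
- *That the primary aim promises proof of benefit in each diagnosis.* Naming MCI and dementia together can simply describe who is enrolled. An average effect in a mixed population is a legitimate target, and broad-entry trials often leave their case mix open.
- *That the low power within dementia is all due to pooling.* Step 3 shows otherwise.

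It is also fair to object that estimates by diagnosis for every outcome and visit would produce many imprecise numbers. That is accepted, and the fix is kept narrower.

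**Conclusion.** The point holds as a mismatch between stated questions and stated analysis. As written, the depression question and the no-improvement assumption, and to a lesser degree the closing clause of the carer hypothesis, would be answered in a mixed population rather than in people with dementia. The direction of harm depends on the statement: a false suggestion of dementia benefit for the depression question, and a false refutation or an unsupported confirmation for the no-improvement assumption.

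The size depends on a mix that the article does not give. The 74%, 56% and 37% rest on an assumed 0.50 SD effect in MCI and none in dementia; the 28% to 14% rest on assumed dementia shares of 50% to 20% and on reading 0.30 as a standardised mean difference. The pooled contrast remains valid as an average over the enrolled mix, so the primary comparison is not undermined. The change should be made, but it concerns wording and one model term, not the design.

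**What to change.** 1. **Secondary outcome measures.** Choose one of two routes. Either reword the depression question, the no-improvement assumption and the carer-relationship clause to the enrolled MCI-plus-dementia population, or keep the dementia wording and base these statements only on the dementia estimate, with its confidence interval, from a model with an arm × diagnosis (× visit) term. Diagnosis is the one already recorded at entry. On either route, a non-significant result should not be presented as showing no improvement.
2. **Analysis, primary outcome.** For GRA versus TAU and COM versus TAU on the ADASCog, report the effect by diagnosis with confidence intervals as a supportive analysis. Word the pooled result as an average over the enrolled mix.
3. **Sample size.** Say that the 80% power at 0.30 refers to the pooled 340 (79% as 170 v 170; 49% as 85 v 85) and not to either diagnosis, and give the expected MCI-to-dementia split if one is intended.

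**Cost.** Rewording costs a few sentences. The model route adds one interaction and, for the ADASCog, two contrasts × two treatment visits × two diagnoses = eight supportive estimates. It needs no extra participants, visits or data. The downside is more estimates with wide intervals (roughly ±0.43 to ±0.67 SD in dementia at the assumed shares), which should be labelled as imprecise.
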